## Materials and methods

2.

### Study design

2.1.

Program acceptability and feasibility will be evaluated with mixed methods using quantitative and qualitative assessments (27). To ensure quality in the research report, we followed the Good Reporting of A Mixed Methods Study (GRAMMS) checklist (28).

### Study setting

2.2.

The study will be conducted in the Portuguese National Network of Integrated Continued Care rehabilitation center. The rehabilitation center provides care for stroke survivors who have recovery potential but cannot return home due to stroke-related impairments after receiving acute care in hospital settings.

### Sampling and recruitment

2.3.

The sampling method selection will be non-probabilistic by convenience. All stroke survivors that comply with the study criteria will be invited to join the program.

We aim to recruit 16 participants taking into account a dropout rate of 25% (29).

Inclusion criteria:

18 years old or above.Clinically diagnosed with ischemic or hemorrhagic stroke.Mild–moderate lower limb paresis with a modified functional ambulation classification (MFAC) of IV (assisted walker) or above.A Montreal Cognitive Assessment (MoCA) score > 20.Able to follow three-step directions.Able to tolerate a minimum of 45 min of exercise.Able to communicate with the investigator, to understand and comply with the study procedures.Show a preference for Portuguese folk dance Vira.Willing and able to provide written informed consent to participate and understand the right to withdraw their consent at any time without prejudice to future medical care.

Exclusion criteria:

Pre-existing neurological, cardiovascular orthopedic, or rheumatic disorder that could interfere with the execution of the proposed protocol;Severe hearing and visual impairment;Poor tolerance to a group setting or significant behavioral problems that would hinder the person from participating.

Two nurses from the rehabilitation center will be responsible for recruitment. In the first stage of recruitment, based on the data in the patient’s clinical file (diagnosis, stage of stroke, presence of hemiparesis, and clinical data), recruiters will identify stroke survivors as potentially eligible participants. In the second stage, a research team member will provide oral and written information regarding the study and recommend to each patient to take at least 24 h to reflect and discuss participation with their relatives/informal caregiver before deciding study to participate.

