In Portugal, musical culture is part of the population’s roots. Portuguese folk dance is a group dance originating from the rural areas of Portugal. It is a movement art combining Portuguese folk songs with traditional folk dance. There are various kinds of dances stemming from different regions of Portugal. Nonetheless, although each dance employs a different technique, there are common traits in the various dances. All dances include circular movements and elaborate footwork, whether they consist of two or three steps, and dance in small circles or long lines (23, 24).

Considering the combination of complex and high-impact movements seen in Tango (15, 16) and Bolero (12) can improve the coordination and balance of patients with stroke, we hypothesize comparable outcomes with Portuguese folk dance.

Since folk dances are deeply rooted in the cultural heritage of a community, we expect that by incorporating a culturally specific intervention, stroke survivors can connect with their cultural identity, fostering a sense of belonging and familiarity. This can enhance motivation and engagement in the rehabilitation process. In addition, cultural activities have the potential to evoke positive emotions, such as joy, pride, and nostalgia (25, 26).

Therefore, engaging in familiar cultural practices, like folk dance, has the potential to reduce feelings of depression, anxiety, and social isolation (25). This positive emotional state can contribute to their overall well-being, motivation, and recovery.

This is the first know study that aims to find scientific evidence connecting Portuguese folk dance to balance and functional mobility improvement in stroke survivors. The implications of this study are manifold, particularly in the context of aging and public health. Aging populations increasingly face the challenges of stroke-related impairments, such as reduced balance and mobility, significantly impacting their quality of life. This study’s focus on stroke survivors addresses a crucial aspect of public health, as stroke incidence tends to rise with age, and effective rehabilitative interventions are essential for enhancing the well-being of this demographic. Therefore, our primary aim will be to assess the acceptability and feasibility of adapted Portuguese folk dance as a post-stroke rehabilitative activity.

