### Intervention

2.4.

The intervention consists of an 8-week program (1-h group training, three times per week). This intervention will supplement the usual care, which consists of daily 45 min sessions of occupational and physical therapy.

The dance style used for this intervention will be an adaptation of the Portuguese folk dance Vira, performed in every region of Portugal. The translation of the name is “twist, turn.” It has a three-step rhythm and is similar to a waltz. First, participants dance in pairs, front-to-front, holding arms in the air without holding hands, forming a circle that moves counterclockwise. At a certain point, half of the participants move to the center, where they tap their right foot and return to their respective places. Then, the circle starts to rotate again, alternating the participants who go to the center (23, 24).

Vira was selected because it combines whole-body movements requiring balance, flexibility, endurance, upper extremity function, perceptual-cognitive skills, and memory. Using Vira’s short routine will allow participants to repeat the dance steps requiring mobilization of attention and memory. In addition, the steps are simple, easy to learn and promote the transfer of weight from one side to the other.

Participants will be taught how to execute movements safely, focusing on maintaining proper alignment, balance, and coordination. Movements will be introduced gradually, allowing participants to build strength, flexibility, and control over time. Due to safety concerns, the dance program will incorporate modifications and adaptations to accommodate individual needs and limitations. Participants will not dance in pairs in this protocol. The instructor will pair participants with poor standing balance with the assistants. The assistants will support the patient by holding hands to increase stability. In addition, participants with poor standing balance will be provided with a gait belt to allow assistants to help them if necessary. We will modify the training for participants with severely reduced balance by dancing in a wheelchair. The instructor will encourage these participants to move their arms and legs, move the wheelchair forward and backward, and perform flexion/extension or lateral flexion of the trunk. The program will take place in a spacious, well-maintained environment with shock-absorbent and non-slip flooring.

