### Data collection

2.5.

Participant characteristics: Participants’ sex, age, educational level, occupation, stroke history, comorbidities, MFAC and MoCA scores will be extracted from the participants’ clinical records.Researchers defined acceptability a priori by four key domains for developing the program and performing a subsequent randomized controlled trial. These key domains include enrollment (number of stroke survivors that participate in the program), retention (number of classes attended and percentage of enrolled participants who completed final program assessments), and satisfaction (assessed with a survey and semi-structured exit interviews).

Safety via adverse events (number of events involving injury).

The study coordinator, who will not be involved in performing the intervention, will administer a customized post-intervention survey to assess participants’ acceptability of the intervention. The questionnaire will consist of Likert scale questions to evaluate the participants’ satisfaction. The interviews aim to gain insight into participants’ perspectives on the intervention’s acceptability and usefulness and identify exercise preferences, barriers, and facilitators that may influence the stroke survivor’s participation in the program.

The following outcome measures will be collected in the week before (T0) and the week after completing the training program (T1) by the following instruments:

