## Conclusion

4.

There is a growing interest in using dance as a therapeutic intervention for stroke survivors. This study aims to establish the acceptability and feasibility of adapted Portuguese folk dance as a post stroke rehabilitative activity. It is possible to identify that the current literature has no studies on the use of Portuguese folk dance in rehabilitation settings. Therefore, this will be the first study to assess this adapted dance program’s feasibility and preliminary effects. The results of this research will contribute to new scientific knowledge, supporting the use of Portuguese folk dance in rehabilitation settings as an effective tool for treating stroke survivors. Ultimately, validating Portuguese folk dance as a tool for rehabilitation settings offers a culturally meaningful and engaging approach to post-stroke care. Such findings can potentially improve stroke survivors’ well-being and foster cross-cultural exchange in stroke rehabilitation practices, thus benefiting aging populations worldwide.

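### Entry requires a preference for the dance under test and enrolment is a count without a denominator, so uptake cannot be read and acceptability applies only to patients who prefer Vira

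*Protocol article*

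**What the plan says.** Five parts of the protocol article bear on this point.

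- **Section 2.3 (Sampling and recruitment)** lists among the inclusion criteria: "Show a preference for Portuguese folk dance Vira". It also states: "All stroke survivors that comply with the study criteria will be invited to join the program". The target reads: "We aim to recruit 16 participants taking into account a dropout rate of 25% (29").
- **Section 2.4 (Intervention)** identifies the tested activity: "The dance style used for this intervention will be an adaptation of the Portuguese folk dance Vira, performed in every region of Portugal".
- **Section 2.5 (Data collection)** defines the acceptability domains, which are meant to inform the programme and a later randomised trial. Enrolment is "enrollment (number of stroke survivors that participate in the program"). The same sentence gives "retention (number of classes attended and percentage of enrolled participants who completed final program assessments"). Satisfaction comes from a survey and exit interviews.
- **The aim and conclusion** are unrestricted. The Introduction says "our primary aim will be to assess the acceptability and feasibility of adapted Portuguese folk dance as a post-stroke rehabilitative activity", and the Conclusion says "This study aims to establish the acceptability and feasibility of adapted Portuguese folk dance as a post stroke rehabilitative activity".
- **The limitations in the Discussion** are the lack of a control group, disease complications and social desirability bias. Selection by preference is not among them.

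**The concern.** Acceptability is part of the primary aim. Two fixed elements of the plan weaken what the study can say about it.

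First, patients who do not prefer the dance cannot enter. They are the patients most likely to find it unattractive, so every acceptability measure taken on participants is conditional on preferring what is being tested. The interviews are meant to identify barriers to participation, but they cannot reach anyone for whom the choice of dance is the barrier.

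Second, a number of participants is not a measure of willingness. It depends on how many suitable patients passed through the centre and for how long recruitment ran. Without the number invited, and the number who would otherwise have been eligible, a high and a low acceptance rate give the same result.

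At stake are the population to which a favourable result applies and the usefulness of the enrolment domain for planning the later trial.

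**Working it through.** **Inputs from the article.** Target 16 and dropout 25% (section 2.3); enrolment as a count, and retention partly as a percentage of enrolled participants (section 2.5); preference for Vira as an entry criterion (section 2.3). The article gives no number screened, eligible, invited or declining, and no share of patients who prefer Vira.

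**The plan's own figure.** 16 × (1 − 0.25) = 12, so 16 is compatible with 12 completers. The base number is not stated, so this is a consistency check only. The figure is not in dispute and the point does not depend on it.

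**Step 1: what a count of 16 can mean.** Uptake = 16 / D, with an exact (Clopper-Pearson) 95% interval. Every D is an assumption.

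| D (assumed) | Uptake | Exact 95% CI |
|---|---|---|
| 16 | 100% | 79 to 100% |
| 20 | 80% | 56 to 94% |
| 40 | 40% | 25 to 57% |
| 80 | 20% | 12 to 30% |
| 100 | 16% | 9 to 25% |

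The enrolment domain as defined reports 16 in every row.

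**Step 2: why enrolled / invited alone is not enough.** Let q be the share of otherwise eligible patients who prefer Vira and c the share of those who consent. Only those with the preference can enrol, so uptake among all otherwise eligible patients is q × c. Assume c = 80%:

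- q = 25%: 0.25 × 0.80 = 20%, and 16 / 0.20 = 80 otherwise eligible patients are needed
- q = 50%: 0.50 × 0.80 = 40%, and 16 / 0.40 = 40 are needed
- q = 75%: 0.75 × 0.80 = 60%, and 16 / 0.60 = 26.7, so 27 are needed

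In each case uptake within the criteria is 80%. It exceeds uptake among all otherwise eligible patients by a factor of 1/q, which is 1.3 at q = 75% and 4 at q = 25%.

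**Step 3: the other acceptability domains.** Let a1 and a0 be acceptability in patients with and without the preference. The value for all otherwise eligible patients is q × a1 + (1 − q) × a0, while the study observes only a1. Assume a1 = 90% and a0 between 20% and 60%:

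- Low end: 0.25 × 0.90 + 0.75 × 0.20 = 0.225 + 0.150 = 37.5%
- High end: 0.75 × 0.90 + 0.25 × 0.60 = 0.675 + 0.150 = 82.5%

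The study would see about 90% in both cases. These values illustrate direction and do not estimate the bias in this trial.

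**Step 4: the two domain definitions side by side.** Retention has a stated denominator, the enrolled participants, and enrolment has none, although both stand in one sentence. The missing denominator therefore affects enrolment only. The preference filter affects all domains.

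**The case against.** The strongest defence is that testing a culturally specific activity in people drawn to it is a legitimate narrower question. The Introduction builds its rationale on familiarity and cultural identity. The study is openly an uncontrolled pilot with a convenience sample. The Vira routine fills 10 minutes of a one-hour session, so liking it does not settle whether inpatients will tolerate three sessions a week for 8 weeks on top of usual care. Screening logs are also often left to a full protocol.

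Much of this stands. The narrower question is sound, and deleting the criterion is a design choice and not a necessity. It does not remove the mismatch, because the stated aim and conclusion are not narrowed. Nor is the count a detail lost in condensing: the article itself defines the domain that way.

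A reader might infer more than the text supports:

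- **That patients are screened on preference before any contact.** The first recruitment stage uses the clinical file, and preference is not among the items named there. The statement that all who comply will be invited cannot fix the order, because the same list includes willingness to consent.
- **That participants will be dance enthusiasts or must have a long-standing preference.** The criterion asks only that a preference be shown.
- **That enrolment is capped at 16.** The article states a target, so a shortfall would still carry some information.
- **That the later trial's recruitment rate will be overestimated.** A count without a denominator yields no rate to overestimate, and the later trial's criteria are not given.
- **That retention shares the missing denominator.** It has its own.

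**Conclusion.** The point holds in a limited form. Enrolment as defined cannot show uptake: over assumed denominators of 100 down to 16, the same count of 16 fits anything from 16% to 100%. Satisfaction, retention and interview findings will apply only to patients who prefer Vira, while the aim and conclusion refer to post-stroke rehabilitation without that restriction and the limitations are silent on it.

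The likely direction is favourable. The size cannot be computed from the document, because neither the share who prefer Vira nor acceptability among the others is given. The factor of 1.3 to 4 for uptake rests on assumed shares of 75% to 25% and on only those with the preference being able to enrol. It is not established that the acceptability result as a whole is determined in advance: participants can still drop out, miss classes or report dissatisfaction.

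**What to change.** 1. **Redefine the enrolment domain** in section 2.5 as two proportions, each with an exact 95% CI: enrolled / invited, and enrolled / otherwise eligible. Patients excluded only for lack of preference for Vira stay in the second denominator. Report reasons for declining.
2. **Keep a log** of patients identified, otherwise eligible, lacking only the preference, invited, declining (with reason) and enrolled. The two nurses already responsible for recruitment can do this. It should start before the first invitation, because refusals not recorded at the time may not be recoverable.
3. **Choose one of two routes for the preference criterion.** Either record preference for Vira at T0 as a descriptor and remove it from the entry criteria, or keep it, restrict every acceptability conclusion to patients who prefer Vira, and add this to the limitations.

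The cost is a small logging burden and edits to one domain definition and to either one criterion or the conclusions and limitations. The downside is that the acceptability figures may be less favourable. The target of 16 does not need to change on this account.

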### Intervention

2.4.

The intervention consists of an 8-week program (1-h group training, three times per week). This intervention will supplement the usual care, which consists of daily 45 min sessions of occupational and physical therapy.

The dance style used for this intervention will be an adaptation of the Portuguese folk dance Vira, performed in every region of Portugal. The translation of the name is “twist, turn.” It has a three-step rhythm and is similar to a waltz. First, participants dance in pairs, front-to-front, holding arms in the air without holding hands, forming a circle that moves counterclockwise. At a certain point, half of the participants move to the center, where they tap their right foot and return to their respective places. Then, the circle starts to rotate again, alternating the participants who go to the center (23, 24).

Vira was selected because it combines whole-body movements requiring balance, flexibility, endurance, upper extremity function, perceptual-cognitive skills, and memory. Using Vira’s short routine will allow participants to repeat the dance steps requiring mobilization of attention and memory. In addition, the steps are simple, easy to learn and promote the transfer of weight from one side to the other.

Participants will be taught how to execute movements safely, focusing on maintaining proper alignment, balance, and coordination. Movements will be introduced gradually, allowing participants to build strength, flexibility, and control over time. Due to safety concerns, the dance program will incorporate modifications and adaptations to accommodate individual needs and limitations. Participants will not dance in pairs in this protocol. The instructor will pair participants with poor standing balance with the assistants. The assistants will support the patient by holding hands to increase stability. In addition, participants with poor standing balance will be provided with a gait belt to allow assistants to help them if necessary. We will modify the training for participants with severely reduced balance by dancing in a wheelchair. The instructor will encourage these participants to move their arms and legs, move the wheelchair forward and backward, and perform flexion/extension or lateral flexion of the trunk. The program will take place in a spacious, well-maintained environment with shock-absorbent and non-slip flooring.

Sessions will be led by a nurse specialized in rehabilitation expert in motor and cognitive exercise programs, and a background as a Portuguese folk dance instructor. We will consider eight stroke survivors as the optimum number of participants per session. Assistance to the instructor will be provided by three nurses that are receiving their master’s training in rehabilitation nursing, using a ratio of two participants for one therapist. In addition, the students will receive training to modify the exercises for each participant when needed and ensure their safety.

To provide a suitable level of challenge, the instructor will progressively increase the difficulty of the workouts accordingly to the participants’ willingness and improved condition. During sessions, the instructor will ask participants about their perceived effort through the Borg Effort Perception Scale (30). All professionals supervising the program application will provide the training’s adaptation, specificity, progression, variation, and safety. The structure of the training sessions is described in detail in Table 1.

**Table 1 tab1:** Structure of the training sessions.

Phase 1: Arrival (10 min)	Social interaction (e.g., greeting friends). A brief discussion on safety issues and how to participate (first-timers). Assess new health and issues linked to the sessions (second-timers).
Phase 2: Warm-up (10 min)	Group warm-up using whole-body amplitude movements incorporating neck, shoulders, hands, trunk, hips and knees movements, and slow passive stretching of the most affected upper extremity using the least affected upper extremity. Essential dance step (e.g., step touch) to increase heart rate. Walking in place or in chair, in a rhythmic routine using music based on group preferences. Voice warm up exercises with loud ahh, glides, and humming exercises.
Phase 3: Technical exercises (Two exercises per session; 10 min)	Trunk rotation. Step-touch side-ways. Moving the hips (side-ways). Weight shifting. Step-touch forward-backward. Basic step of the meringue. Sliding to the side. Twist.
Phase 4: Directed improvisation (10 min)	Participants will move freely according to some directions (bilateral movements only, large and big movements, etc.). In turn, they must either guide and be followed or follow the sequence proposed by another participant.
Phase 5: Dance routine (10 min)	Instructor will perform the routine, acting as a model for the participants. Integration of the dance routine with music. During the first 2 weeks, the sessions will focus on balance, requiring participants to form a circle, hold their arms in the air and transfer weight from one leg to the other. These moves will be followed by a couple of steps forward to reach the center of the circle, tap one of their feet and return to the starting position. From the third to the fifth week, in addition to the initial steps, participants will rotate 360° before moving to the center of the circle. In the last stage, participants will dance in a circle that moves counterclockwise.
Phase 6: Relaxation (5 min)	Active slow amplitude movements with music, stretching, and breathing exercises.
Phase 7: Session Assessment (5 min)	Brief group discussion to gather participant feedback on each exercise to guide future sessions.

